## Abstract

**Background:**

eRAPID (electronic patient self-Reporting of Adverse-events: Patient Information and aDvice) is an internet based system for patients to self-report symptoms and side effects (adverse events or AE) of cancer treatments. eRAPID allows AE reporting from home and patient reported data is accessible via Electronic Patient Records (EPR) for use in routine care. The system can generate alerts to clinical teams for severe AE and provides patient advice on managing mild AEs. The overall aims of eRAPID are to improve the safe delivery of cancer treatments, enhance patient care and standardise AE documentation.

**Methods:**

The trial is a prospective randomised two-arm parallel group design study with repeated measures and mixed methods. Participants (adult patients with breast cancer on neo-adjuvant or adjuvant chemotherapy, colorectal and gynaecological cancer receiving chemotherapy) are randomised to receive the eRAPID intervention or usual care over 18 weeks of treatment. Participants in the intervention arm receive training in using the eRAPID system to provide routine weekly adverse event reports from home. Hospital staff can access eRAPID reports via the EPR and use the information during consultations or phone calls with patients.

Prior to commencing the full trial an internal pilot phase was conducted (*N* = 87 participants) to assess recruitment procedures, consent and attrition rates, the integrity of the intervention information technology and establish procedures for collecting outcome data. The overall target sample for the trial is *N* = 504.

The primary outcome of the trial is quality of life (FACT-G) with secondary outcomes including health economics (costs to patients and the NHS), process of care (e.g. contacts with the hospital, number of admissions, clinic appointments and changes to treatment/medications) and patient self-efficacy. Outcome data is collected at baseline, 6, 12, 18 weeks and 12 months. The intervention is also being evaluated via end of study interviews with patient participants and clinical staff.

**Discussion:**

The pilot phase was completed in February 2016 and recruitment and attrition rates met criteria for continuing to the full trial. Recruitment recommenced in May 2016 and is planned to continue until December 2017. Overall findings will determine the value of the eRAPID intervention for supporting the care of patients receiving systemic cancer treatment.

**Trial registration:**

Current Controlled Trials ISRCTN88520246. Registered 11 September 2014.

## Background

Systemic drug treatments for cancer (chemotherapy, hormonotherapy, biological therapy, targeted agents) are associated with significant adverse events (AEs). An AE is an untoward symptom or disease associated with (but not necessarily causally related to) a medical treatment or intervention AEs may lead to changes in drug dosage, cessation of treatment and can significantly compromise patients’ quality of life. Severe AEs can escalate to hospitalisation for potentially life-threatening toxicities: 18% of cancer patients present to emergency services within 14 days of a scheduled hospital visit for symptom management (infection, fever, nausea/vomiting, pain, breathlessness) [1–4]. Patients with breast, gastrointestinal, colorectal cancers and those with metastatic disease are amongst those most likely to have emergency admissions [4, 5].

Many patients however, delay seeking care especially out of hours [3, 5]. This concurs with the findings of a UK enquiry into patient outcome and death (National Confidential Enquiry into Patient Outcome and Death, NCEPOD) which found that of patients dying within 30 days of systemic cancer therapy, 17% delayed seeking advice for over 24 h [6]. AEs are documented consistently by physicians in clinical trials however in routine care recording of AEs by clinicians and reporting by patients is variable and often omitted [6]. It has been recognised for some time that a structured AEs reporting system would be useful to facilitate correct documentation and grading of AE severity to support tailored management. Consequently, the National Cancer Institute (NCI) in the US have developed the Common Terminology Criteria for Adverse Events (CTCAE v 4.0) [7] as a reporting and severity grading system for cancer clinical trials. These have recently been adapted for patients to self-report (NCI-PRO CTCAE) [8] and these items have concordance with nurse evaluated AE [9] and similar items created for self-report correlate with quality of life measures [10]. The need for routine monitoring of cancer treatment AE is at odds with a health care system relying increasingly on patient self-management and home based care. In order to bridge the gap in service provision to detect, identify and manage AE in cancer patients the Electronic patient self-Reporting of Adverse-events: Patient Information and aDvice (eRAPID): system was developed [11].

### Patient reported outcome measures (PROMs)

PROMs have been used in clinical practice to support care of individual patients, recent reviews suggest they improve symptom/function monitoring, physician patient communication and decision making [12–17], can save time during clinic visits and improve the accuracy of symptom reporting [18]. In the UK the 2008 Darzi report [19] recommended that collection of PROMs data should be an essential component of health care evaluation [19] and the Department of Health (DOH) subsequently produced guidelines to aid their implementation [20]. Following this, use of PROMs in the health service is most advanced in England (particularly for performance comparisons) [21]. Two recently published reports by the Independent Cancer Taskforce and NHS England have continued to highlight the need to put PROMs at the centre of strategies to improve patient centred cancer care and quality of life [22, 23].

### Electronic and mobile reporting technology

Electronic reporting of patient reported outcome measures (PROMs) has proven extremely acceptable to patients in the clinic setting [24–26]. Examples of successful implementation of electronic symptom reporting in oncology clinical practice include PatientViewpoint [27], the symptom tracking and reporting system (STAR) system for patients to report chemotherapy AE [28] and the Tell Us™ [29] system for advanced cancer patients in hospices undergoing palliative care (all in the U.S.). In Austria the Computer-based Health Evaluation System (CHES) software [30] has been developed and an interactive online system (ISAAC) is in use in Canada [31]. In the UK the ASyMS mobile phone system is currently being evaluated [32]. Electronic patient reported outcome systems have proven very acceptable even for patients coping with extreme symptom burden and reduced quality of life; indeed a mean monthly PROM completion rate of 83% at 34 weeks has been achieved with patients receiving cancer treatment [33].

### eRAPID development work

The eRAPID research programme was designed to develop and evaluate an online system to support the collection and clinical integration of patients’ symptom/AE reports during cancer treatment. It utilises a web-based questionnaire builder system called QTool. QTool Version 1 was originally used in a large prospective study of cancer survivors, recruiting 636 patients in 12 months, 81% of whom completed web-based questionnaires at baseline [34] (www.epocs.leeds.ac.uk), confirming the feasibility of web-based patient-reporting and QTool acceptability. Between 2010 and 2013 the eRAPID developmental work was conducted (funded by an National Institute of Health Research grant: Programme Development Grant scheme RP-DG-1209-10,031), which focused on:

Developing the electronic platform to allow QTool data to be securely linked to the electronic patient records used by Leeds Teaching Hospitals (see Fig. 1).Selection, adaption and evaluation of items for patients to report symptoms and AE resulting in the development of patient-reported AE (PRAE) items based on CTCAE grades [35]. The initial item pool includes most common AEs namely nausea, vomiting, diarrhoea, mucositis, fatigue, insomnia, palmar-plantar erythema, pain, peripheral neuropathy, appetite loss, constipation, rash, bleeding, anaemia, febrile neutropenia and stoma problems.Collating patient information and advice on AE management***.*** We reviewed and compiled the extensive literature available providing patient advice on the management of common symptoms and side effects during systemic cancer treatment. The information is available on the password protected eRAPID patient website. The eRAPID QTool symptom report provides patients with immediate brief graded advice dependent on severity of AE reported (including a recommendation to contact the hospital when severe symptoms are detected) and links users out to the eRAPID website for more detailed information. The website has been extensively reviewed by both patients and oncology staff.Mapping patient care pathways. With support from staff responsible for monitoring chemotherapy patients at St James’ Institute of Oncology, Leeds the current care pathways for patients receiving systemic treatment were mapped to establish where eRAPID can best fit. This work was conducted via: staff interviews, a local audit of care pathways/acute triage processes, mapping the existing chemotherapy pathways for the detection and management of AE and an assessment of patient experience of acute admissions and prospective patient interviews and diaries during chemotherapy to record AEs and costs to patents and services. The latter aimed to develop a questionnaire for health economic analysis [5].

**Fig. 1 Fig1:**
[figure not shown]
eRAPID system overview

This developmental work led to the:Successful mapping of current systemic treatment pathway, establishing where eRAPID is best placedIdentification of staff requiring training to deliver eRAPIDAdaptation of a health economic questionnaire for cancer patients receiving treatment

### The eRAPID intervention

An overview of the eRAPID intervention is described in Figs. 1, 2a and b. Figure 1 represents the technical components and their integration to support reporting of AEs immediately available in the EPR. The architecture protects patient confidentiality providing security whilst allowing immediate linkage to individual patient records to support care.

**Fig. 2 Fig2:**
[figure not shown]
**a** Screenshots of eRAPID intervention (Patient login and symptom reports). **b** Screenshots of eRAPID intervention- Clinician view of symptom reports in electronic patient record (EPR)

The intervention consists of the following components:Patients can log in to QTool (using a unique username and password) to access the eRAPID symptom questionnaire anywhere with internet access (including home or hospital).For mild/moderate problems information about self-managing these issues are provided via brief instructions in QTool along with hyperlinks to more detailed advice on the eRAPID patient website (Fig. 2a).Where severe symptoms are reported patients are advised to contact the hospital.The patient reported data is immediately available for staff to view in the individuals’ electronic patient records in Leeds Teaching Hospitals NHS Trust (Patient Pathway Manager, PPM). See Fig. 2b.Alerts for severe symptom reports are sent directly to staff via email. Clinicians can then log into PPM and view the patients’ symptom reports and take appropriate action where needed.

Prior to the start of the current trial the eRAPID system underwent usability testing with *N* = 14 breast cancer patients receiving adjuvant or neo-adjuvant chemotherapy and relevant staff.

### Hypotheses

We hypothesise the eRAPID intervention has the potential to bring benefit to patients, staff and the NHS in the following ways:Benefits for patients○ Earlier symptom detection and improved self-management, timely admissions○ Improved supportive medication use○ Appropriate hospital, GP, community contacts○ Better outcomes (improved symptom control, functioning and quality of life)
Benefits for staff○ Reduce the number of hospital, GP, community contacts○ Save time spent on enquiring and recording AEs○ Focus attention during clinical contacts on most important or severe AEs○ Support decision making in routine care
Benefits to the NHS○ eRAPID provides a cost-effective approach to support patient self-management and reduce hospital and GP contacts

### Study design

This study is a single centre 1:1 allocation prospective randomised two-arm parallel group trial design with repeated measures and mixed methods.

### Patient sample

The study sample includes patients with gynaecological or colorectal cancer requiring chemotherapy, or breast cancer undertaking either neo-adjuvant or adjuvant following systemic treatment pathways at St. James’s Institute of Oncology, Leeds, UK.

## Methods

Participants are randomised to either the intervention arm (eRAPID plus usual care) or the control arm (usual care). See Fig. 3 for the trial flow diagram. Participants are on the study for an 18 week period from the start of chemotherapy. A subset of participants (where feasible within the funding timeframe) will also be assessed at a 12 month time point to examine any potential longer term impact of the intervention on quality of life and clinical processes.

**Fig. 3 Fig3:**
[figure not shown]
Trial flow diagram

### Usual care

Includes an initial consultation with an oncologist to decide whether to commence systemic treatment. Patients are provided with verbal and written information on treatment benefits and expected AEs, and are given instructions on how to contact the hospital. They have a nurse assessment before starting their treatment. During treatment patients are routinely assessed in clinics for AE and to prescribe their next cycle of treatment by an oncologist, Clinical Nurse Specialist (CNS) or staff grade doctor. Depending on AE experienced by the patient, treatment doses can be reduced, and/or supportive medications changed (e.g. anti-sickness drugs, anti-diarrhoea drugs). When at home if patient has a serious AE they are asked to contact the hospital and the nurse dealing with the patient phone call uses an Acute Triage Form to record reasons for the call, document the AE and gives advice.

### eRAPID intervention

In addition to usual care, participants randomised to the eRAPID intervention arm will receive training on using the system and will be asked to complete the eRAPID symptom report routinely from home at least weekly and when they experience symptoms over 18 weeks during treatment. Clinicians are given access to patients’ self-reported AEs via the electronic patient record system (PPM) and asked to utilise the information when seeing patients in clinic or providing telephone advice.

### Aims and study objectives

To evaluate the potential benefits of eRAPID for patients and staff, the intervention and usual care arm will be compared on the following areas through the collection of appropriate clinical information, patient reported outcomes and interview data:Assessment of hypothesised benefits to patients with mild or moderate AE:
Number of hospital, GP and community contacts during the studyImproved patient reported outcomesImproved symptom detection and supportive medication use
2.Assessment of hypothesised benefits to patients with severe AE:
Improved detection and treatment of AEs and admissions (e.g. number of clinician alerts generated from eRAPID, number of admissions and hospital contacts)Levels of morbidity (percentage of planned chemotherapy received, changes to treatment plans (dose reductions, dose delays/interruptions)).
3.Assessment of hypothesised benefits to clinicians: Staff will be interviewed about their views of the value of eRAPID in saving time currently spent enquiring and recording patients’ AE and supporting treatment decision-making. In addition oncologists will complete a feedback form at routine review appointments after seeing eRAPID intervention participants to assess how/if patient reports are used.4.Monitor patient safety, assessed by monitoring acute admissions, cumulative deaths and cause of death.

The FACT-G Physical Wellbeing Score [36] (measured at 18 weeks) is the primary outcome. The main secondary outcome is cost effectiveness assessed via use of health care services (including hospital admissions, telephone contacts and consultations, medication and personal expenses). In addition participant records will be linked to costs held within the local pilot database of the National Patient-Level Information and Costing System (PLICS) scheme. This provides a cost for hospital based accident and emergency department visits, outpatient attendances and inpatient stays.

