13-item scale for measuring the level of patient engagement in their healthcare (knowledge, skill and confidence for self-management)	Statements rated on 4 point scale from disagree strongly to agree strongly and additional N/A option.	• When all is said and done I am the person who is responsible for taking care of my health	Baseline, 18 weeks and 12 months
		• I am confident I follow through on medical treatments I may need to do at home	
	Responses are combined to provide a single score of between 0 and 100 with higher scores representing higher levels of patient activation.	• I know what treatments are available for my health problems.	
	Scores can be classified into one of four groups, known as ‘levels of activation’.		
Secondary outcomes- eRAPID/IT system performance			
System Usability Scale (SUS) [42]			
10 item instrument to assess views of usability of an IT systems.	Each statement rated from 1 strongly disagree to 5 strongly agree.	• I think that I would like to use this system frequently	18 weeks
		• I thought there was too much inconsistency in this system	
	Responses are calculated into a total score ranging from 0 to 100 with higher scores representing better system usability.	• I felt very confident using the system	
eRAPID end of study questionnaire			
15 statements/free text boxes to assess participant views of using eRAPID and suggestions for improvements	Statements rated on 3–5 response option scales (e.g. very easy-very difficult) and free text boxes for comments.	• How easy or difficult was it to learn how to use the eRAPID system?	18 weeks
		• How did you feel about the amount of time it took to complete the symptom questions?	
		• To what extent do you feel that the symptom questionnaire was useful for the doctors and nurses you saw during your treatment?	
		• Have you got any suggestions about how the eRAPID system could be improved?

**Table 2 Tab2:** eRAPID RCT in systemic cancer treatment: Researcher collected data for secondary outcomes

Data	Description of data	Time point for collection
Treatment and clinical information	• Cancer diagnosis, stage and grade	Initial baseline assessment and reviewed for changes at 18 weeks
	• Age, date of birth	
	• Baseline data on planned chemotherapy	
	• Changes to treatment delivery and reason	
	• Comorbidities	
Clinical process- Hospital contacts	• Contacts with the hospital e.g. (unplanned) telephone, appointments, consultations	• Data extracted from medical notes for 18 of study

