### Sample size calculations

The sample size for the full trial is based on the primary patient outcome of better symptom control measured at 18 weeks by the FACT-G. A sample of 176 patients per arm is necessary to detect a 2-point change in the FACT-G Physical Wellbeing score with 80% power and 5% significance, where the population standard deviation is 6.7. This change corresponds to a medium Cohen’s effect size (0.3) [43].

Allowing for 30% attrition, a minimum of 252 patients per arm (504 total) is required. With potentially >500 eligible patients treated in the cancer centre annually, we expect to recruit 20 patients per month over approximately 24–30 months, allowing for 70% internet access and 70% consent rate.

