### Primary outcome

The FACT-G Physical Well-being score will be summarised overall and by treatment arm. Changes in score over time and differences between treatment arms will be explored using a multilevel repeated measures model. The model for each post-randomisation point will be adjusted for baseline score and stratification factors. If there are missing items, subscale scores will be prorated as per the FACT-G scoring manual.

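### The week-18 primary score may be read after planned chemotherapy has ended for participants on shorter plans, which could dilute an on-treatment effect; the planned model does not use planned chemotherapy length

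*Protocol article*

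**What the plan says.** All references are to the protocol article.

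- **Endpoint.** Under Aims and study objectives: "The FACT-G Physical Wellbeing Score [36] (measured at 18 weeks) is the primary outcome". The sample size section describes the target as the "primary patient outcome of better symptom control measured at 18 weeks by the FACT-G".
- **Clock.** Under Methods: "Participants are on the study for an 18 week period from the start of chemotherapy".
- **Eligibility.** The inclusion criteria set a floor of three months of planned chemotherapy cycles when consent is given. No upper or typical length is stated.
- **Intervention period.** In the abstract, participants are "randomised to receive the eRAPID intervention or usual care over 18 weeks of treatment". In the eRAPID intervention section, the symptom report is to be completed "routinely from home at least weekly and when they experience symptoms over 18 weeks during treatment".
- **Model.** The Primary outcome section plans a multilevel repeated measures model: "The model for each post-randomisation point will be adjusted for baseline score and stratification factors". The stratification factors under Randomisation are cancer site, gender and, for gynaecological patients, previous chemotherapy.
- **Data collected.** FACT-G is taken at baseline, 6, 12 and 18 weeks (Table 1). Table 2 lists "Baseline data on planned chemotherapy".

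**The concern.** For a participant at the eligibility floor these statements do not fit together. The planned course ends before week 18, so the reporting period cannot be 18 weeks during treatment, and the only powered reading falls after planned treatment.

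The intervention is meant to work by detecting and managing adverse events of treatment. Once treatment is over, there may be less for it to improve. The week-18 score could then mix on-treatment symptom control in participants on longer plans with post-treatment recovery in the others. Planned length is neither a stratification factor nor a stated covariate. Differences in score between the two groups that baseline score and stratification factors do not explain would therefore go into residual variance, and the groups could by chance be unevenly split between arms.

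At stake is the reading of a small or null week-18 difference: it could mean no benefit, or a benefit during treatment that had partly faded by the time of measurement.

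**Working it through.** **1. The stated sample size.** Inputs from Sample size calculations: difference 2 points, SD 6.7, 80% power, 5% significance (taken as two-sided).

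n per arm = 2 × 6.7² × (1.960 + 0.842)² / 2² = 176.2, against 176 stated. Power at 176 per arm: the standard error is 6.7 × √(2/176) = 0.714 and 2/0.714 = 2.80, which gives 80.0%. For 30% attrition, 176/0.70 = 251.4, so 252 per arm and 504 in total. The figures reproduce.

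**2. The timing gap.** Three months is 3 × 365.25/12/7 = 13.0 weeks, and 18 − 13.0 = about 5 weeks (6 if three months is counted as 12 weeks). This is the gap at the floor; longer plans have a smaller gap or none.

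**3. Possible dilution.** Let f be the share whose plan ends before week 18 and r the fraction of the effect they keep at week 18. Neither is in the documents, so both are assumed. The average difference is 2 × [1 − f(1 − r)]. Unadjusted power at 176 per arm, SD 6.7:

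| f | r = 0 | r = 0.5 |
|---|---|---|
| 10% | 1.8 points, 71% | 1.9 points, 76% |
| 20% | 1.6 points, 61% | 1.8 points, 71% |
| 30% | 1.4 points, 50% | 1.7 points, 66% |

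**4. What raises these figures.**

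- *Baseline adjustment, which is planned.* With baseline correlation c (assumed), the SD becomes 6.7 × √(1 − c²): 5.80 at c = 0.5 and 5.36 at c = 0.6. At f = 20%, r = 0, power is then about 73% and 80%, instead of 61%.
- *Lower attrition.* At the pilot's 15%, 252 × 0.85 = about 214 per arm are analysed. Unadjusted power is 87% undiluted and, with r = 0, 79% at f = 10%, about 70% at f = 20% and 58% at f = 30%.

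**5. Would averaging the three visits be a better primary contrast?** With between-visit correlation 0.5 to 0.7 (assumed), the variance of the mean is (1 + 2ρ)/3 = 0.667 to 0.800 of the single-visit variance.

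- *Full 2 points at weeks 6 and 12, none off treatment at week 18.* At f = 30% the average effect is (2 + 2 + 1.4)/3 = 1.80 and power is 80% to 87%, against 50% for week 18 alone.
- *Effect building linearly (0.67, 1.33, 2.0 points; assumed).* With no dilution the average is 1.33 and power is 55% to 63%, against 80% for week 18. At f = 30% the average is (0.67 + 1.33 + 1.4)/3 = 1.13 and power is 43% to 49%, against 50%.

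Averaging therefore helps or harms according to how the effect develops, which the documents do not say.

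**The case against.** A reader might infer that toxicity has ended by week 18 for participants on short plans, that the effect is therefore diluted, and that the trial is underpowered. The documents do not support that.

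- No section says how long toxicity lasts after the last cycle. The adverse events listed under eRAPID development work include fatigue and peripheral neuropathy, which could persist. Dose delays and interruptions are among the outcomes, so treatment may run past its planned end.
- Three months is a floor. The references to 18 weeks of treatment suggest that the authors expected most plans to span the window, so the affected share could be small.
- The sample size section specifies a 2-point mean difference at week 18. It does not claim that every participant carries the full effect. Power falls only if the true week-18 mean difference is below 2 points.
- Arm differences at weeks 6 and 12 come from the planned model, so a null result at week 18 would not be uninterpretable.
- A fixed reading at the end of the intervention period, under intention to treat, is a legitimate choice. Extra covariates and supportive contrasts are often left to an analysis plan, and that plan is not shown.

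All of this stands against a claim of certain dilution or a wrong power figure. Two things remain: the passages do not agree for participants near the floor, and the adjustment set that the article does state leaves out recorded baseline information that bears on the primary reading.

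**Conclusion.** The mismatch is in the protocol's own text and holds. Participants on shorter plans may be measured after planned treatment has ended, by about 5 weeks at the minimum, and this could dilute an on-treatment effect. The direction rests on the assumption that benefit is smaller off treatment. The size cannot be fixed from the documents: the 50% to 76% range is conditional on assumed shares of 10% to 30% and none to half of the effect kept, and it is conservative because it ignores the planned baseline adjustment and uses the full 30% attrition.

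The stated 80% power needs no correction. Nor is there a case for replacing week 18 by the average over visits as the primary contrast: under a building effect the average loses power, and it would change the primary outcome of a trial already recruiting. What is justified is a reconciliation of the text and a cheap improvement to the model and its supportive estimates.

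**What to change.** 1. Keep week 18 as the primary time point.
2. Add to the primary repeated-measures model an indicator for planned chemotherapy ending before week 18 (yes/no), with its interaction with visit. Define it from the plan recorded at baseline, not from treatment received, so that the comparison stays randomised.
3. Pre-specify two supportive estimates from the same model: the week-18 arm difference within each baseline-defined group (this needs the arm terms for that group), and the arm difference averaged over weeks 6, 12 and 18.
4. Reconcile the abstract's and the intervention section's descriptions of 18 weeks of, or during, treatment with the eligibility criterion, and state the expected share of participants still on planned treatment at week 18. Which wording is right is for the sponsor to decide.

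The data are already collected, and no visits or patients are added. The cost is a few degrees of freedom. The subgroup estimates will be imprecise and should be reported as supportive only.
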